### Study endpoints

The primary endpoint of the study is the occurrence of a first relapse within 12 months (week 52) after first presentation. Relapse is defined as having proteinuria (3+ on urine dipstick confirmed by >200 mg/mmol creatinine on quantitative urinalysis) for three consecutive days.

Secondary endpoints can be found in box 2.Box 2Secondary endpoints are being compared between the intervention groupsTime to first relapse (days).Relapse rate over 2-year period (n/year).Cumulative steroid dose over 2-year period (mg/m^2^).Number of (serious) adverse events (n).Number of treatment discontinuations (n).Proportion patients with FRNS or SDNS (%).Days of missing school (days), outpatient visits (n), hospitalisation days (days).HRQoL and psychosocial adaptation at different time points (see table 1):Cross-sectional and longitudinal.Comparison with healthy peers and other chronic diseases.FRNS, frequent relapsing nephrotic syndrome; HRQoL, health-related quality of life; SDNS, steroid-dependent nephrotic syndrome.

### Sample size

Sample size was calculated based on the superiority design of the trial, as well as on the intention-to-treat principle and on the primary outcome of the study: occurrence of relapse within 12 months after first presentation. To achieve a power of 80% with a two-sided significance level of 5%, two groups of 41 subjects are needed to identify a reduction in relapse of 30% (from 75% relapse to 45%), which is considered clinically relevant. A total of 82 patients need to complete 2 years of follow-up. With an estimated drop-out rate of 10%, 92 patients in total need to be included for the RCT. It is expected that around 90% of all children with a first episode of INS will be steroid sensitive.^22 23^ Additionally, we expect that about 65% of the patients screened for eligibility are willing to participate.^4^ In conclusion, this means a total of 157 patients need to be recruited. With an incidence of 60 new cases of INS per year in the Netherlands and 30 new cases per year in Belgium (estimated), an inclusion period of 2 years is expected. After withdrawal of informed consent, no study subjects will be replaced.

### Recruitment

When patients present in one of the participating hospitals (see online supplement 2) with a first episode of INS, they will be informed about the RCT, after which they receive further written information about the RCT. When a patient presents with a first episode of INS in a non-participating hospital, the coordinating study team is contacted. The treating paediatrician will explain the study briefly and, if patient and parents agree, they will receive further written information by email. If interested in participating in the trial, the patient will be referred to the nearest participating hospital. After 4 weeks, patients will be checked if remission has been achieved. If so, informed consent for the RCT will be obtained and when the patient meets all of the inclusion criteria and none of the exclusion criteria, he/she will be randomised (figure 2).

10.1136/bmjopen-2018-027011.supp2Supplementary data

**Figure 2 F2:**
[figure not shown]
CONSORT flowchart of study design. CONSORT, Consolidated Standards of Reporting Trials.

To make sure all paediatricians in non-participating centres are acquainted with the trial, a monthly reminder by email will be sent. Also, additional information about the study for paediatricians, general practitioners, parents and patients (as well as all patient information forms (PIFs)) will be available on the study website (www.learns.nl). For questions, they can contact the coordinating investigator.

### Randomisation

A total of 92 eligible patients will be randomly assigned to one of the two treatment arms in a 1:1 ratio, receiving either levamisole (treatment) or placebo (control) added to standard corticosteroid treatment. Block randomisation will occur using block sizes of 2, 4 and 6, which will be randomly used in order to make concealment of allocation as accurate as possible while granting minimal differences in numbers between the two groups. Randomisation (week 4) will be performed by the local investigator using CastorEDC. The local investigator is blinded for the outcome of randomisation; only members of the AMC clinical pharmacy have rights to view allocation of treatment. Patients, parents, medical and nursing staff, outcome assessors, monitors and data analysts are blinded to treatment allocation.

Treatment allocation will be blinded until the study has ended, all data has been collected, queries have been resolved and the database has been locked.

### Data collection and management

Patient data will be collected at every visit by the local investigator and/or coordinating investigator. Clinical data will be entered in the Good Clinical Practice compliant electronic data management system CastorEDC. Additionally, patients are asked to keep a diary on treatment compliance, adverse events, relapse (proteinuria) and days of illness and school absence. These data will also be collected on the electronic case report form. Questionnaires on HRQoL will be completed at home at scheduled time points on the KLIK website (www.hetklikt.nu). After registering, parents receive a reminder to fill out questionnaires.

### Statistical analysis

The outcomes of all included study subjects will be analysed as intention-to-treat. For safety analysis, an ‘as treated’ population will be defined. Study subjects who are lost to follow-up, withdraw informed consent or stopped study medication prematurely will be analysed according to allocated treatment group (figure 2). All data that have been collected until withdrawal or lost to follow-up will be used for analyses. Missing values at baseline and/or follow-up will not be imputed. R Studio will be used for performing all statistical analyses. A p value of <0.05 will be considered statistically significant. Continuous data will be presented as means with SD or median with IQR, depending on distribution. For between group comparisons, a Student’s t-test in case of normal distribution or Mann-Whitney U test in case of non-normal distribution will be used. Categorical data will be presented as proportions and compared using a χ^2^ test. The primary outcome, the occurrence of a relapse at 1 year after first presentation, will be compared between groups using a χ^2^ test. Relapse-free survival will be presented as a Kaplan-Meier survival curve. Multivariate analyses (age at onset, sex, ethnicity, time to remission and FRNS/SDNS) will be performed using Cox regression.

No interim analysis for either efficacy or futility will be performed. Safety reviews will be performed by the Data Safety Monitoring Board (DSMB) after 1 year or when 25 patients have been included and have completed the 24 weeks (week 28 after first presentation) using study medication.

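### The primary chi-square test has no stated place for children lost relapse-free before week 52, and the likely ways of placing them bias the risk difference modestly if dropout differs by arm

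*Protocol article*

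**What the plan says.** Under Study endpoints, the protocol article defines the primary endpoint as a first relapse by week 52. Under Statistical analysis it names a chi-square test for relapse at 1 year and fixes these rules:

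- "The outcomes of all included study subjects will be analysed as intention-to-treat"; children who are lost, withdraw or stop study drug are analysed in the arm to which they were allocated.
- On partial follow-up: "All data that have been collected until withdrawal or lost to follow-up will be used for analyses".
- On gaps in the data, the rule is: "Missing values at baseline and/or follow-up will not be imputed".

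Kaplan-Meier appears there only to present relapse-free survival, and Cox regression only for multivariate analyses. Under Sample size, the calculation is said to rest on the intention-to-treat principle, and "A total of 82 patients need to complete 2 years of follow-up". The allowance for losses is then stated: "With an estimated drop-out rate of 10%, 92 patients in total need to be included for the RCT". Withdrawals are not made up: "After withdrawal of informed consent, no study subjects will be replaced".

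**The concern.** A 2×2 table needs a yes or a no for each child. A child last seen relapse-free at, say, week 20 has neither.

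- **Leave the child out.** The test no longer covers all included children, and the child's follow-up is not used in it. If relapses seen before dropout are kept, as the all-data rule implies, only relapse-free children are removed and the observed relapse rates rise.
- **Count the child as no relapse.** This is a single imputation, which the article rules out, and it lowers the observed rates.
- **Count the child as a relapse.** This is also an imputation, and it raises the rates.

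The two errors run in opposite directions and do not cancel between arms when dropout is unequal. This is the trial's only powered comparison. With no rule fixed, the handling could be chosen after the data are seen.

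**Working it through.** **1. The plan's own figure.** The inputs come from Sample size: "To achieve a power of 80% with a two-sided significance level of 5%, two groups of 41 subjects are needed". The relapse risks assumed there are 0.75 on placebo and 0.45 on levamisole, a difference of 0.30. With pooled variance and p̄ = 0.60:

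n = [1.960·√(2·0.60·0.40) + 0.842·√(0.75·0.25 + 0.45·0.55)]² / 0.30² = (1.358 + 0.555)² / 0.09 = 40.7, so 41 per arm.

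Then 82/0.9 = 91.1, so 92. Both figures reproduce. The inflation to 92 treats dropouts as lost to the primary test, while Statistical analysis says that they are analysed.

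**2. The choice can matter.** This illustration is assumed and is an upper case: 41 completers and 5 relapse-free dropouts per arm, relapses 31 v 22, uncorrected chi-square.

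- Excluded: 31/41 v 22/41, p = 0.038.
- Counted as no relapse: 31/46 v 22/46, p = 0.058.
- Counted as relapse: 36/46 v 27/46, p = 0.043.

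**3. Size of the bias.** Assumptions: constant relapse hazard from week 4, dropout independent of relapse, and a fraction d of each arm leaving at a uniform time in weeks 4–52. For true risk p:

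- λ = −ln(1−p), and g = p/λ is the chance of still being relapse-free at dropout.
- Lost relapse-free: u = d·g.
- Relapses seen: r = (1−d)p + d(1−g) = p − d(p − 1 + g).
- Counted as no relapse, the estimate is r. With relapse-free losses excluded and seen relapses kept, it is r/(1−u).

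Placebo, p = 0.75: λ = 1.386, g = 0.541, p − 1 + g = 0.291. Levamisole, p = 0.45: λ = 0.598, g = 0.753, p − 1 + g = 0.203.

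Placebo minus levamisole in percentage points (differences taken before rounding):

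| Dropout, levamisole / placebo | Counted as no relapse | Relapse-free losses excluded |
|---|---|---|
| 10% / 10% | 72.1 − 43.0 = 29.1 | 76.2 − 46.5 = 29.7 |
| 15% / 5% | 73.5 − 42.0 = 31.6 | 75.6 − 47.3 = 28.3 |
| 5% / 15% | 70.6 − 44.0 = 26.6 | 76.9 − 45.7 = 31.2 |

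Simulation of the same model agrees to about 0.1 point.

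**4. Dropout spread over 2 years.** The article ties the 10% to 2-year completion. If dropout is uniform over weeks 4–104, a share of 48/100 falls before week 52, so d is multiplied by 0.48. The differences become (counted as no relapse, then excluded): 29.6 and 29.9 at 10%/10%; 30.8 and 29.2 at 15%/5%; 28.4 and 30.5 at 5%/15%.

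**5. Children affected at 10%/10%.** All dropout before week 52: 46 × 0.10 × (0.753 + 0.541) = 3.5 + 2.5, about 6 of 92. Spread over 2 years: 0.48 × 6, about 3 of 92.

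**6. Power and type I error.** Simulation of 20,000 trials with 46 per arm, all dropout before week 52. Power:

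| Dropout, levamisole / placebo | No relapse | Excluded | Strict completers | Kaplan-Meier, log-log |
|---|---|---|---|---|
| 10% / 10% | 81% | 82% | 81% | 83% |
| 15% / 5% | 87% | 78% | 81% | 82% |
| 5% / 15% | 73% | 86% | 81% | 83% |

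Strict completers means dropping every child who leaves early, including those whose relapse was seen. The Kaplan-Meier difference averaged 30 points in each pattern. With 75% relapse in both arms, the log-log test rejected in 4.8% to 5.2% of trials under these patterns. Counting losses as no relapse rejected in 4.8% to 6.3%.

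**The case against.** The strongest reply is that the text can be read consistently. Intention-to-treat may mean only that children are counted as allocated. No imputation then points to a chi-square on available outcomes, and partial follow-up enters the Kaplan-Meier curve and the Cox model. The inflation from 82 to 92 fits that reading. It is possible, but the wording about all included children and about lost and withdrawn children goes against it. It also leaves open whether relapses seen before dropout stay in, and that decides whether the available-data test is biased. A fuller analysis plan may settle this; the rules stated in the article do not.

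Several further points against the concern stand:

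- A reader might infer that about 10% of children are affected. The 10% refers to 2-year completion, and only relapse-free losses before week 52 matter.
- A reader might infer that relapse drives withdrawal and so makes the missing outcomes unequal between arms. A child who relapses and then leaves already has the primary outcome, and the Intervention section stops study treatment at relapse, not follow-up. Unequal dropout is an assumption here.
- A reader might infer that no chi-square test is valid. A strict completers-only test is unbiased under independent dropout, with about 81% power. Its fault is that it discards relapses that were observed, against the all-data rule.
- A reader might expect a clear power gain from Kaplan-Meier. The log-log test has about 83%. The untransformed Greenwood test reaches 84%, but its type I error can come close to 6%.

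**Conclusion.** The concern holds as a moderate issue. Under the rules as written, a child lost relapse-free before week 52 cannot be placed in the primary table without breaking one of them. The two likely handlings bias the risk difference when dropout differs by arm. For a true 30 points the estimates range from 26.6 to 31.6 at a 15%/5% split in either direction, with all dropout before week 52. The range is 28.4 to 30.8 if dropout is spread over 2 years. At equal dropout of 10% the error is 1 point or less.

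These figures rest on a constant hazard, independent uniform dropout and assumed splits between arms that keep the planned 10% overall. A reader might infer a serious inflation of type I error. That is not supported at plausible splits: counting losses as no relapse rejects 9.4% of the time only with 20% v 0% dropout, all before week 52, and about 6% if the same dropout is spread over 2 years. The sample size arithmetic is correct and does not need to change.

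**What to change.** Make the primary comparison the difference between arms in Kaplan-Meier relapse risk at week 52. Include all 92 randomised children, censored at withdrawal or loss. Test on the log-log scale with Greenwood variance, and give log-log confidence intervals for each arm and an interval for the difference built from them. The endpoint, the week-52 horizon and N stay the same, and power is about 83%.

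Narrow the no-imputation sentence so that it does not block a pre-specified sensitivity analysis that counts relapse-free losses before week 52 as relapses. Fix both changes before unblinding.

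The cost is a few sentences and a few lines of code. There are two downsides: the headline test is no longer a simple chi-square, and Kaplan-Meier assumes non-informative censoring, which is why the sensitivity analysis is needed. If the chi-square test is kept, the least that is needed is one sentence saying how children lost before week 52 are handled, both those with a relapse already seen and those without.

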### Objectives

The primary objective of the study is to investigate the effect of additional levamisole to standard steroid therapy in comparison with placebo from 4 to 28 weeks (figure 1) after the start of the first episode of steroid-sensitive INS (SSNS) in children (age 2–16 years) on the occurrence of any relapse within 12 months after first presentation.

Secondary objectives are:To investigate differences between the two study groups in time to first relapse, the number of relapses, cumulative steroid dosage and the occurrence of SDNS and FRNS in a 2-year period.To investigate HRQoL, psychosocial adjustment, parental distress at different stages of treatment (longitudinal and cross-sectional) and to identify medical and personal factors related to HRQoL.To investigate the consequences of the disease on days of missing school for children, (financial) problems for parents, outpatient visits and hospital admissions.

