### Questionnaires

To investigate the effect of INS on the HRQoL, psychosocial adaptation, school performance and parental distress, parents and patients (if 8 years and older) will be asked to complete HRQoL questionnaires at five different time points: at first presentation, at 4 weeks after presentation (prednisolone only), at 28 weeks after presentation (after study treatment), at 1 year after presentation (primary endpoint) and at 2 years after presentation (end of study). Different validated HRQoL questionnaires will be used (table 2).^13–15^ The Paediatric Quality of Life Inventory Generic Scale 4.0 consists of both self and proxy reports including a broad age range (2–18 years).^13^ Norm scores for a Dutch healthy norm population and for children with other chronic illnesses (eg, asthma) are available.^16 17^ The Strength and Difficulties Questionnaire (SDQ) assesses the psychosocial adjustment of children and adolescents.^14 18 19^ Lastly, the Distress Thermometer for Parents is a brief screening instrument to identify distress and everyday problems in parents of children with a chronic condition.^15 20^ In addition, general questionnaires regarding demographics, medication and compliance will be sent to all parents and/or children. KLIK (*Dutch*: Kwaliteit van Leven In Kaart) is a web-based platform for HRQoL questionnaires, developed by the Psychosocial Department of our hospital and used by over 10 000 patients and 400 healthcare professionals.^21^ It is used for both daily clinical care and research in a broad paediatric field. In this study, the KLIK website (www.hetklikt.nu) will be used for filling out the questionnaires; it will only be used for research purposes. In contrast to daily clinical use, the patient will not receive feedback by his or her treating physician. After registration on the website, parents and, if applicable, patients of 8 years and older receive a reminder by email 7 days prior to their next visit.

**Table 2 T2:** Overview of quality of life questionnaires used per age range. At each time point, all questionnaires are provided

Age range	2–3 years	4 years	5–7 years	8–10 years	11–12 years	13–16 years
	Parent about parent	Parent about parent	Parent about parent	Parent about parent	Parent about parent	Parent about parent
Sociodemographics*	General	General	General	General	General	General
Parental distress†	DT-P	DT-P	DT-P	DT-P	DT-P	DT-P

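### The unadjusted two-sample tests given for continuous outcomes leave the pre-randomisation HRQoL scores unused and cannot deliver the longitudinal HRQoL comparison that the protocol lists

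*Protocol article*

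**What the plan says.** The Statistical analysis section of the protocol article has one rule for comparing continuous data between groups: a Student's t-test "in case of normal distribution or Mann-Whitney U test in case of non-normal distribution will be used". It names no baseline covariate. The one adjusted analysis is given as "Multivariate analyses (age at onset, sex, ethnicity, time to remission and FRNS/SDNS) will be performed using Cox regression". The same section rules out imputation of missing baseline or follow-up values.

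Box 2 (Study endpoints) says that the secondary endpoints are compared between the intervention groups. Its last entry is "HRQoL and psychosocial adaptation at different time points (see table 1):Cross-sectional and longitudinal". The Objectives section likewise asks for longitudinal and cross-sectional study of HRQoL, psychosocial adjustment and parental distress.

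The Questionnaires section schedules five assessments: first presentation, week 4 on prednisolone alone, week 28 after study treatment, and then "at 1 year after presentation (primary endpoint) and at 2 years after presentation (end of study"). The Randomisation section states "Randomisation (week 4) will be performed by the local investigator". Two scores per child are therefore planned before study drug and three after.

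Table 2 shows that the PedsQL is parent-reported up to age 7 and child-reported from age 8. The SDQ has a different parent form below age 4 and adds a child form from age 11. The parental distress thermometer (DT-P) is completed by both parents where applicable.

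**The concern.** A t-test or Mann-Whitney test compares one value per child. Used on a follow-up HRQoL score, it takes no account of where that child stood at week 4, although the score is planned. It also cannot describe how the arm difference develops over weeks 28, 52 and 104, which is what a longitudinal comparison means. The Cox regression does not fill the gap: it models time to an event and lists no HRQoL covariate.

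At stake is precision. The trial is small and powered only on relapse, and children aged 2 to 16 can be expected to differ widely in HRQoL. In such a setting a child's own earlier score is usually the cheapest source of precision. Improved HRQoL is part of the trial's stated hypothesis, and the HRQoL study was added at the request of the patient association, so a needlessly wide interval on this endpoint would be a loss.

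**Working it through.** **Inputs from the document.** 41 per arm, two-sided 5%, 80% power, relapse 75% versus 45%, 10% drop-out, 92 randomised (Sample size); 1:1 allocation and randomisation at week 4 (Randomisation).

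**Inputs assumed.** The correlation r between a pre-randomisation score and a follow-up score is not given; 0.3 to 0.7 is used. For the power figures, a true difference of 0.5 SD is also assumed. All results use the normal approximation, one visit, complete forms and one common scale.

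**The plan's own figure.** For two proportions with pooled variance and no continuity correction:

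n = [1.960 × √(2 × 0.60 × 0.40) + 0.842 × √(0.75 × 0.25 + 0.45 × 0.55)]² / 0.30² = 40.7, rounded up to 41 per arm.

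82 / 0.9 = 91.1, rounded up to 92. Both stated figures reproduce and are not in dispute. The document gives no SD, target difference or power for HRQoL.

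**Unadjusted test at one visit.** Detectable difference = (1.960 + 0.842) × √(2/41) = 2.802 × 0.2209 = 0.62 SD. A Mann-Whitney test on normal data (relative efficiency 0.955) gives 0.62 / √0.955 = 0.63 SD.

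**Adjusted for one baseline score.** The residual variance is multiplied by 1 − r², so the detectable difference is 0.619 × √(1 − r²) and the equivalent number per arm is 41 / (1 − r²).

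| r | 1 − r² | Fall in standard error | Detectable difference | Equivalent n per arm | Power for 0.5 SD |
|---|---|---|---|---|---|
| unadjusted | 1 | – | 0.62 SD | 41 | 62% |
| 0.3 | 0.91 | 5% | 0.59 SD | 45 | 66% |
| 0.5 | 0.75 | 13% | 0.54 SD | 55 | 74% |
| 0.7 | 0.51 | 29% | 0.44 SD | 80 | 89% |

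**Both pre-randomisation scores.** Adjusting for the mean of weeks 0 and 4, with all correlations equal to r, multiplies the variance by 1 − 2r²/(1 + r). Power for 0.5 SD is then 68%, 79% or 94% for r = 0.3, 0.5 or 0.7.

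**All 92 children assessed.** With 46 per arm the unadjusted detectable difference is 2.802 × √(2/46) = 0.58 SD. The relative gains from adjustment are the same.

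**The case against.** The strongest reply is that the quoted sentence does not name HRQoL. It is a general rule, and it suits the endpoints in Box 2 that have no baseline value, such as cumulative steroid dose or hospital days. The section also gives no method for other HRQoL aims, such as factors related to HRQoL or comparison with healthy peers. An article condenses, and the HRQoL model may well be in a document not shown. This stands in part. A reader might infer that the repeated measures are discarded on purpose, or that a separate test is planned at each visit. The document says neither, and its objectives point to a longitudinal analysis. What remains is that Box 2 promises a between-group HRQoL comparison and only one method for continuous between-group comparisons is stated.

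The second reply is that an unadjusted test is sound under randomisation. That stands fully: it is unbiased and keeps its error rate, and chance imbalance at week 4 is already covered by that error rate.

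The third reply is that the gain rests on an unknown correlation. Week 4 follows acute onset and a course of daily prednisolone, so its correlation with week 52 or 104 may be low. This also stands. At r = 0.3 the gain is only 5% of the standard error.

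Finally, a plain week-4 covariate has its own faults. Without imputation it drops every child who lacks that form, and the reporter can change as a child turns 8. These objections are right, and they shape the fix below.

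**Conclusion.** The point holds as a cheap improvement to a stated method. As written, the unadjusted tests do not match the longitudinal HRQoL endpoint and leave the week-0 and week-4 scores unused. The loss at one visit is 0.62 SD detectable against 0.59, 0.54 or 0.44 SD for assumed correlations of 0.3, 0.5 or 0.7. These figures rest on 41 complete forms per arm on one scale. Changes of form or reporter would weaken the correlation and reduce the gain.

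A reader might infer that the HRQoL results would be biased or that the trial's conclusion is at risk. Neither follows: HRQoL is one of several secondary endpoints, the article says openly that only the primary outcome is powered, and the relapse analysis is untouched.

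**What to change.** For the between-arm comparison of PedsQL, SDQ and DT-P, replace the unadjusted tests with a linear mixed model for repeated measures:

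- Follow-up at weeks 28, 52 and 104, with arm, time, arm-by-time and age.
- Week 4 named as baseline and modelled jointly as an outcome, with the arm means constrained to be equal there. Children without a week-4 form are then kept, and the no-imputation rule is respected.
- For PedsQL and SDQ, a term for form version and reporter (parent or child).
- For DT-P, a parent-within-child effect.
- The arm difference with a 95% confidence interval at each follow-up time.

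The data are already scheduled, and allocation stays blinded until database lock, so the change can be made without knowledge of results. The cost is analysis wording, some analyst time, and reliance on a missing-at-random assumption. If an analysis plan already specifies a model of this kind, bring the Statistical analysis section into line with it.

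### The primary relapse comparison is valid but unadjusted, and the only adjusted model described includes a post-randomisation outcome

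*Protocol article*

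**What the plan says.** The Statistical analysis section fixes the primary test: "The primary outcome, the occurrence of a relapse at 1 year after first presentation, will be compared between groups" with a chi-square test. It mentions no covariates for that test.

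Covariates appear later in the same paragraph, for a Cox regression: "Multivariate analyses (age at onset, sex, ethnicity, time to remission", with FRNS/SDNS closing the list. The section also says that values missing at baseline will not be imputed.

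The Sample size section matches the unadjusted test. It begins "To achieve a power of 80% with a two-sided significance level of 5" per cent, and then states "two groups of 41 subjects are needed to identify a reduction in relapse of 30" percentage points ("from 75% relapse to 45" per cent). It adds: "With an estimated drop-out rate of 10%, 92 patients in total need to be included for the RCT".

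Box 1 makes remission within 4 weeks of steroids an entry criterion, and the Randomisation section places allocation at week 4. Age at onset and time to remission are therefore both settled before allocation. Box 2 lists the proportion with FRNS or SDNS as a secondary endpoint, and the Objectives section places it in the 2-year period.

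**The concern.** The authors picked two baseline variables for modelling and left them out of the comparison that decides the trial. If these variables predict relapse, an unadjusted test uses less of the available information than it could, and any chance imbalance in them stays in the main result.

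The Cox model does not fill the gap. Box 1 excludes children with a previous episode, so no child can have FRNS or SDNS at randomisation. That status develops through relapses, which are what levamisole is meant to prevent, so conditioning on it can absorb part of the treatment effect. The article thus describes no treatment comparison adjusted for baseline factors alone.

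Precision matters here because the Discussion names the size of the study population as an important limitation and considers pooling with another trial if inclusion falls short.

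**Working it through.** **1. The plan's own figure.** Inputs from the Sample size section: 75% and 45% relapse, two-sided 5%, 80% power. Mean rate = (0.75 + 0.45)/2 = 0.60. The pooled-variance formula without continuity correction is

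n = [1.960 × √(2 × 0.60 × 0.40) + 0.842 × √(0.75 × 0.25 + 0.45 × 0.55)]² / 0.30²

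= [1.960 × 0.693 + 0.842 × 0.660]² / 0.09 = 3.66 / 0.09 = 40.7, so 41 per arm.

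Drop-out: 82/(1 − 0.10) = 91.1, so 92. Both figures reproduce. Power of the unadjusted test is 80.3% at 41 per arm and 84.8% at 46.

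**2. Power with adjustment.** The article gives no prognostic strength, so it is varied as an assumption. Trials were simulated at 41 per arm with overall rates held at 75% and 45%. The uncorrected chi-square test was compared with the treatment term in a covariate-adjusted logistic regression. The 1,500- and 6,000-trial sets use one normally distributed baseline score; the 20,000-trial set uses two covariates. Entries are power in %, unadjusted → adjusted.

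| Log-odds per SD | 1,500 trials | 6,000 trials | 20,000 trials |
|---|---|---|---|
| 0 | – | 82.1 → 80.7 | 81.4 → 80.6 |
| 0.2 | – | – | 81.5 → 81.0 |
| 0.3 | – | 80.9 → 80.1 | – |
| 0.4 | 82 → 83 | – | 82.0 → 82.5 |
| 0.5 | – | 81.9 → 82.4 | – |
| 0.7 | 81 → 84 | – | 81.4 → 84.2 |
| 0.8 | – | 81.3 → 84.3 | – |
| 1.0 | 80 → 87 | 81.4 → 86.3 | 81.8 → 87.1 |
| 1.3 | – | 81.8 → 89.2 | – |

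Monte Carlo standard error near 80% power is √(0.8 × 0.2/1,500) = 1.0 point for the smallest set, 0.5 for 6,000 trials and 0.3 for 20,000. With no treatment effect, the 6,000-trial set rejected in 4.7% to 5.9% of trials unadjusted and 4.4% to 5.2% adjusted.

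**3. Cross-check.** If the covariates explain a share R² of relapse variance, the effective size is about n/(1 − R²).
- R² = 5%: 41/0.95 = 43.2 per arm, power 82.4%.
- R² = 10%: 41/0.90 = 45.6 per arm, power 84.4%.
- R² = 15%: 41/0.85 = 48.2 per arm, power 86.4%.

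In the simulation, log-odds of 0.5, 0.8 and 1.0 correspond to R² of about 4 to 6%, 10 to 12% and 15 to 17%, so the two methods agree.

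**4. Variance estimator.** In the 6,000-trial set, a linear-model risk difference with a conservative robust standard error (HC3) had power of 79.4% at log-odds 0 and 85.6% at 1.0, somewhat below the logistic test.

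**5. Chance imbalance.** Assume allocation is not stratified by the factor, with 46 per arm. A factor present in half the children then differs between arms by at least 10 points with probability about 30%, at least 15 points about 14%, and at least 20 points about 6%. If the factor shifted relapse risk by 20 points (assumption), a 15-point imbalance would move the observed difference by 0.15 × 20 = 3 points, against a target of 30.

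**The case against.** The strongest reply is that nothing here is an error. The chi-square test is valid under randomisation, the sample size was computed for that test, and the two agree. That stands, so the point is about efficiency and clarity.

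Second, the benefit is assumed. The covariate list also contains sex and ethnicity and makes no claim about prognosis. If age and time to remission predict little, adjustment gains nothing and may cost about a point. Time to remission is also confined to the first 4 weeks by the entry criteria, which may limit what it can explain. This stands too, and it is why the result is given as a range.

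A reader might go further and infer three things that the documents do not support.
- *That power is being lost as a matter of fact.* No prognostic strength is given, so a loss is possible but not shown.
- *That the trial has no margin.* The 82 children are those needed to complete 2 years, whereas the primary endpoint falls at week 52. If all 92 contribute a primary outcome, power is about 85%.
- *That randomisation is unstratified.* The article says "Block randomisation will occur using block sizes of 2, 4 and 6" and names no stratification factor, but it condenses a fuller protocol that is not shown, and silence is not a statement. The point does not depend on it.

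Incomplete covariates are also unlikely to matter much, since age and remission within 4 weeks are entry criteria.

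**Conclusion.** The point holds as a worthwhile improvement to a valid plan. The article fixes an unadjusted primary test, and its one multivariable model mixes baseline factors with an outcome of the disease course after randomisation. As described, no analysis gives a treatment effect adjusted for baseline factors only.

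The size depends on unknown prognostic strength. At 41 per arm, power changes by about 1 point down to no change if the two factors predict weakly or not at all, rises by about 3 points at log-odds of 0.7 to 0.8 per SD, and rises by about 5 to 7 points at 1.0. These figures assume the design rates of 75% and 45% and a correctly specified logistic model. Adjustment would correct chance imbalance in age at onset and time to remission, and in no other factor.

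**What to change.** Before unblinding, prespecify the following.
- The primary effect is the week-52 relapse risk difference adjusted for age at onset and time to remission, from logistic regression with standardisation over all randomised children.
- The model contains no post-randomisation covariate; FRNS/SDNS in particular is left out of any model meant to estimate the treatment effect.
- The test that gives the p value and the variance estimator that gives the interval are named. The power figures above are for the treatment term in the logistic model.
- A rare missing baseline covariate is filled by a simple imputation that ignores treatment. This needs an exception to the current statement that baseline values will not be imputed.
- The unadjusted chi-square test is reported as supportive.

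The design and sample size stay as they are. Both covariates are already needed for the planned Cox model, so the cost is wording, slightly more analysis work, and up to about 1 point of power if the covariates predict nothing.
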